**3.6. Blinding of the Study**

Only the investigator responsible for performing the treatments (who will open the randomization envelopes) will know which treatment is assigned to each participant. This investigator will reveal the identification of each group to all involved in the study after the statistical analysis of the data.
Therefore, the investigator responsible for data collection and their assistant will be blinded to the treatments assigned to the groups. The participant and the statistician will also be blinded to the type of treatment received.

**3.7. Avaliações pré-tratamento**

After receiving the necessary explanations, participants affected by actinic keratosis who sign the Informed Consent Form (ICF) will undergo anamnesis and complete the AKQoL and Face-Q questionnaires, as well as the data collection form for the study, which will involve counting, classifying, and mapping the facial lesions. These data will be collected by the principal investigator (calibrated). Photographic records of the lesions will also be taken using a Quantificare® 3D camera and the camera of an iPhone 11 Pro Max. Following these evaluations, the treatment will be conducted according to the randomization.

**3.8. Anamnese**

Anamnesis will be conducted with participants from all groups. In addition to questions related to the participant’s general health, demographic data (age, gender, marital status, occupation, education level, living conditions, family income) and medical history (main complaint, current disease status, medical history, medications) will be collected.

**3.9. Experimental Design**

Immediately before the lesion treatment, the investigator responsible for the treatment will retrieve and open one envelope (without altering the numerical sequence of the remaining envelopes) and proceed with the indicated procedure. Participants will be allocated to the experimental groups as follows:

**G1** - Control Group (gold standard – 16% MAL with 3-hour incubation) (n=36) – participants will be treated with topical 16% MAL photosensitizer (Metvix®, Galderma [ANVISA Registration No. 1291600650016](https://consultas.anvisa.gov.br/#/medicamentos/25351002042200468/)) with a 3-hour incubation period. The light source used for skin illumination will be a visible light source (LED) with a wavelength of 643nm (Hygialux LLT1601®, KLD - ANVISA Registration No. 10245239012).

**G2** - Experimental Group (optimized time using gold standard MAL 16% with shorter incubation time – 1 hour) (n=36) – participants will be treated with topical 16% MAL photosensitizer (Metvix®, Galderma – [ANVISA Registration No. 25351.002042/2004-68](https://consultas.anvisa.gov.br/#/medicamentos/25351002042200468/)) with a 1-hour incubation period. The light source used for skin illumination will be a visible light source (LED) with a wavelength of 643nm (Hygialux LLT1601®, KLD - ANVISA Registration No. 10245239012).

**G3** - Experimental Group (compounded medication with lower concentration – 8% MAL with conventional incubation time of 3 hours) (n=36) – participants will be treated with topical 8% MAL photosensitizer (compounded by StinPharma – a compounding pharmacy with industrial standards) with a 3-hour incubation period. The light source used for skin illumination will be a visible light source (LED) with a wavelength of 643nm (Hygialux LLT1601®, KLD - ANVISA Registration No. 10245239012).

**G4** - Experimental Group (compounded medication with lower concentration – 8% MAL with shorter incubation time of 1 hour) (n=36) – participants will be treated with topical 8% MAL photosensitizer (compounded by StinPharma – a compounding pharmacy with industrial standards) with a 1-hour incubation period. The light source used for skin illumination will be a visible light source (LED) with a wavelength of 643nm (Hygialux LLT1601®, KLD - ANVISA Registration No. 10245239012).

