Wiegell et al. (2009) compared PDT mediated by MAL containing different concentrations (16% versus 8%) in participants with actinic keratosis in symmetrical areas of the face or scalp. In this study, the participants applied the product in the hospital and were instructed to expose themselves to sunlight for the remainder of the day. The average exposure time was 244 minutes, and the total average effective fluence was 30 J/cm². The results showed no significant difference between the groups after three months of treatment: complete lesion response was 76.9% in the MAL 16% group and 79.5% in the MAL 8% group. A linear association was observed between the increase in light dose and a better response in all participants. However, among the 26 participants who received a total effective dose greater than 8J/cm², no relationship was found between an increment in response and an increase in the total dose.

Braathen et al. (2009) evaluated the effect of incubation time, one hour versus three hours, MAL concentration (8% and 16%), and lesion preparation for actinic keratosis treatment. They conducted a multicenter, open, randomized, parallel-group study with a sample composed of 110 participants with 380 previously untreated lesions on the face and scalp. The lesions were debrided, and MAL cream (8% or 16%) was subsequently applied before red light illumination (570-670 nm; light dose, 75 J/cm²). The participants were followed for two to three months. Sixty participants (54%) were retreated and evaluated at six months. The results showed that the overall complete response (CR) rates (after 1 or 2 PDT treatments) were slightly higher after PDT using a 3-hour incubation with MAL 16% compared to other regimens (85% vs. 76% with 1 hour, 16%; 74% with 1 hour, MAL 8%; and 77% with three hours, MAL 8%). For lesions on the face/scalp, CR rates were maintained across all severity ranges (thin, moderate, and thick lesions) after treatment with 1-hour MAL 16% (CR rates ranging from 74 to 86%) or 3 hours MAL 16% (87–96%). The lesion recurrence rates at 12 months after two treatments were similar (19% with one hour vs. 17% with three hours with MAL 16%) and lower for MAL 8% (44-45%).

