**3.5. Randomization**

To randomly assign participants to the experimental groups, a random draw of 144 numbers will be conducted using the website <https://www.sealedenvelope.com/>. The group distribution will be identical (1:1:1:1) for the four groups. The distribution will be carried out in blocks (24 blocks of 6 participants). Opaque envelopes will be labeled with sequential numbers, and inside each envelope will be information regarding the corresponding experimental group, according to the order obtained in the draw. The envelopes will be sealed and will remain unopened in numerical order until the time of lesion treatment. The draw and preparation of the envelopes will be performed by an individual not involved in the study. Immediately before the treatment of the lesions, the investigator responsible for the treatment will open the envelope (without altering the numerical sequence) and will proceed with the indicated procedure.

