**3.9.1. Treatment with Topical MAL Photosensitizer**

Before the treatment, the treated area will be cleansed with 0.2% aqueous chlorhexidine. Following this, a light curettage will be performed on the facial area using a sterile curette.

After curettage, a thin layer of the photosensitizer, approximately 1 mm thick, will be applied to the affected areas of the participant's face. An occlusive dressing will then be applied to enhance the penetration of 8% or 16% MAL. This dressing will be covered with aluminum foil to protect from light, preventing ambient light from influencing the protoporphyrin production process.

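### As most naturally read, the protocol has the allocation envelope opened before curettage, and nothing requires lesion preparation to be finished before the arm is known

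*Protocol*

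**What the plan says.** Section 3.5 (Randomization) sets the timing of allocation: "The envelopes will be sealed and will remain unopened in numerical order until the time of lesion treatment". At that time the treating investigator "will open the envelope (without altering the numerical sequence) and will proceed with the indicated procedure". Section 3.9 (Experimental Design) repeats the rule: "Immediately before the lesion treatment, the investigator responsible for the treatment will retrieve and open one envelope".

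Section 3.6 (Blinding of the Study) says that the investigator who performs the treatments and opens the envelopes is the only person who knows the arm. The data collector, the assistant, the participant and the statistician are stated to be blinded.

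Section 3.9.1 (Treatment with Topical MAL Photosensitizer) then gives the steps. First: "Before the treatment, the treated area will be cleansed with 0.2% aqueous chlorhexidine". Then: "Following this, a light curettage will be performed on the facial area using a sterile curette". The cream goes on after curettage. The section names no operator for the curettage and sets no standard for its extent beyond calling it light.

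Section 3.7 places the lesion count, classification, mapping and photographs before treatment.

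**The concern.** Curettage is controlled by hand and is identical by design in all arms. It therefore belongs on the blinded side of the allocation wherever that is possible, and here it is possible. If the operator already knows that a participant will get 8% rather than 16%, or 1 hour rather than 3, the vigour of the curettage can vary with the arm, knowingly or not.

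The protocol's own background gives reason to take the step seriously. The Contextualization section describes an earlier randomised study as having examined incubation time, concentration "and lesion preparation for actinic keratosis treatment". It also cites a review that lists omitting curettage among the ways to reduce pain, bleeding and exudation.

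The outcomes exposed are complete remission, the adverse effects in the diary, the pain score and analgesic use (section 3.10). Masking the assessor protects how outcomes are measured, not how the lesions were prepared. The analysis cannot adjust for the extent of curettage either, since the protocol does not provide for recording it.

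**Working it through.** The protocol attaches no figure to this point, and the order of steps does not alter the stated 36 participants per group. The check is therefore a reading of the sections against one another.

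1. **When is the envelope opened?** Sections 3.5 and 3.9 agree: immediately before lesion treatment, after which the indicated procedure follows.

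2. **Does treatment include curettage?** Three things say yes.
   - Curettage is described in section 3.9.1, whose heading calls the whole sequence treatment. It is not in section 3.7, which covers the pre-treatment assessments.
   - The Contextualization section describes the classic regimen as made up of curettage and MAL application followed by illumination.
   - The same section, reporting the trial of one versus two sessions, counts surface debridement as part of each treatment.

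   One thing says no: section 3.9.1 places cleansing before the treatment, with curettage following cleansing. On that usage, treatment could mean the cream alone.

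3. **Who performs the curettage?** Section 3.9.1 is in the passive voice. Section 3.6 says that the person who opens the envelopes performs the treatments. If curettage is part of treatment, its operator knows the arm.

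4. **What follows under each reading?**
   - Treatment includes curettage: the envelope is opened first and lesions are prepared with the arm known.
   - Treatment means the cream only: the envelope may be opened after curettage, but no sentence says that it must be.

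   Under neither reading does the protocol exclude knowledge of the arm during curettage.

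5. **How tightly is each step fixed?**
   - Cream layer: approximately 1 mm (section 3.9.1).
   - Incubation: 1 or 3 hours (section 3.9.1.1).
   - Light: 75 J/cm² over 1,570 s (Table 1).
   - Curettage: one adjective, with no end point and no record.

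   Of the steps listed, curettage is the least tightly specified. It is also the only one of them that can be completed before allocation is known.

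**The case against.** The strongest reply is that the order is not stated. Cleansing is said to come before the treatment, the curettage operator is not named, and an envelope opened just before the cream would already give the sequence asked for here. That stands. A reader might infer that the protocol prescribes opening the envelope before curettage; it does not say so in terms. It is the more natural reading, and the alternative is nowhere required.

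A reader might also infer a size from the background figures, by taking the single-treatment response of 93% in thin and 70% in thicker lesions as what extra scraping could gain, and setting it against the 85% versus 74–77% reported for the four regimens. The documents do not support this. In the first study every treatment included debridement, so the gap arose between lesion types that had all been debrided. It does not show that more curettage makes a thick lesion respond like a thin one. The light dose there was 37 J/cm², against 75 J/cm² here. The second set of figures is after one or two treatments, whereas this trial gives one session. Both are rates per lesion, whereas the objective in section 2.2 is 100% remission relative to the initial facial count.

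Nor is it shown that an operator would compensate in the 8% or 1-hour arms. Favouring the arm labelled gold standard is equally conceivable. The background names lesion preparation as a factor studied but reports no result for it.

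Some protection already exists. Baseline counts and photographs precede treatment, late opening of the envelope helps concealment, the written curettage instruction is common to all arms, and outcome assessors are stated to be blinded. These protect the baseline, enrolment and outcome assessment. They do not make curettage blind to the arm.

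**Conclusion.** The point holds as a gap in the sequence of trial conduct. As most naturally read, sections 3.5, 3.9 and 3.9.1 have an operator who knows the arm carry out an operator-dependent, unrecorded step that is common to all arms, and no section forbids it. This is an avoidable opening for performance bias in remission, pain and local reactions.

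Its size and direction are unknown from the documents, and no estimate should be quoted. The conclusion rests on two assumptions: that treatment in sections 3.5 and 3.9 includes the steps described in section 3.9.1, and that the treating investigator does the curettage. If either is wrong, what remains is that the order and the operator are left open, and the same clarification settles both. The point does not show that the trial's comparisons will be biased. It shows that one source of bias can be closed almost for free.

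**What to change.** Amend sections 3.5 and 3.9 to give one explicit order:

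1. Complete the baseline lesion count, mapping and photographs.
2. Confirm eligibility.
3. Cleanse and curette.
4. Open the next numbered envelope.
5. Apply the assigned cream and start the incubation clock.

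In section 3.9.1, use the word treatment consistently with this order and name who performs the curettage.

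The cost is a few sentences. No extra staff, visit or procedure is needed, and no dose, incubation time or clinical rule changes. Both concentrations must be at hand when the envelope is opened.

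The fix is partial. Cream application, occlusion and wiping follow allocation and remain unblinded to the operator, so performance bias is reduced rather than eliminated, and the trial report should say so.

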**2. OBJECTIVES**

**2.1. General Objective**

The objective of this study is to compare the efficacy of the topical application of methyl aminolevulinate (MAL) in concentrations of 8% and 16%, mediated by red light, and to evaluate the impact of different incubation times (1 or 3 hours) in the treatment of actinic keratoses on the face, with a 12-month follow-up.

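### Concentration is fully aliased with product (marketed 16% cream, compounded 8% cream), so the 8% versus 16% result cannot be attributed to concentration alone

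*Protocol*

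**What the plan says.** Protocol section 2.1 (General Objective) sets two questions, and the Abstract repeats them. The first is about strength: "compare the efficacy of the topical application of methyl aminolevulinate (MAL) in concentrations of 8% and 16%, mediated by red light". The second is about time: "evaluate the impact of different incubation times (1 or 3 hours".

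Section 3.9 (Experimental Design) defines the four arms, 36 participants each:

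- **G1** (16%, 3 h): "participants will be treated with topical 16% MAL photosensitizer (Metvix®, Galderma".
- **G2** (16%, 1 h): the same marketed cream, labelled "optimized time using gold standard MAL 16% with shorter incubation time".
- **G3** (8%, 3 h): "compounded medication with lower concentration – 8% MAL with conventional incubation time of 3 hours".
- **G4** (8%, 1 h): "compounded medication with lower concentration – 8% MAL with shorter incubation time of 1 hour".

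For G3 and G4 the source is the same single pharmacy: "topical 8% MAL photosensitizer (compounded by StinPharma – a compounding pharmacy with industrial standards". There is no arm with a compounded 16% cream, and no 8% cream is said to be in the marketed vehicle.

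The Results Analysis section names a two-way ANOVA for normally distributed data, without naming its factors, and chi-square, Fisher or likelihood ratio tests for categorical variables.

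**The concern.** The four arms look like a 2×2 factorial of strength by incubation time. In fact a third attribute, the product, moves in step with strength. Lower clearance in the 8% arms could come from the lower strength, from the formulation, or from the amount of active substance actually present. Similar clearance would support only this particular compounded cream, not 8% MAL in general. The same holds for tolerability, where the Justification reasons from lower concentration to lower cost and fewer adverse effects.

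The Protocol itself gives reasons why formulation could matter. The Contextualization section attributes MAL's advantage over ALA to better penetration, and describes the marketed product as a lipophilic cream with a limited time in use after opening. Section 3.9.1 adds occlusion to enhance penetration. No vehicle, stability data or assayed content is given for the 8% cream. At stake is what the trial may conclude on the first half of its stated objective.

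**Working it through.** **1. Arms side by side (section 3.9)**

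| Arm | n | Strength 16% (C) | 3 h (T) | Marketed product (P) |
| --- | --- | --- | --- | --- |
| G1 | 36 | 1 | 1 | 1 |
| G2 | 36 | 1 | 0 | 1 |
| G3 | 36 | 0 | 1 | 0 |
| G4 | 36 | 0 | 0 | 0 |

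Columns C and P are identical (correlation 1.0). A design matrix with intercept, C, T and P has four columns but rank 3, so separate effects of C and P are not estimable.

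**2. What each contrast estimates**

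Let c, p and t be the effects of strength, product and time, and let ct and pt be their interactions with time:

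- G1 − G3 (at 3 h) = c + p + ct + pt
- G2 − G4 (at 1 h) = c + p
- (G1 − G3) − (G2 − G4) = ct + pt
- G1 − G2 (within the marketed cream) = t + ct + pt
- G3 − G4 (within the compounded cream) = t

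Every contrast between strengths carries c and p together. The interaction carries ct and pt together. The two time contrasts are each made within one product and carry neither c nor p as a main effect.

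**3. Sample size does not help**

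Section 3.1 plans 36 per group from response rates of 64% and 91%, 95% confidence and 80% power. With a two-sided chi-square test without continuity correction (sidedness assumed):

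n = [1.96·√(2·0.775·0.225) + 0.842·√(0.91·0.09 + 0.64·0.36)]² / 0.27² ≈ 36.4, rounded up to 37.

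Power at 36 per group is 79.6%. The stated figure is thus essentially reproduced and is not at issue. More participants would estimate c + p more precisely, but would not divide it.

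**4. Illustration of a wrong attribution (assumed inputs only)**

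Suppose the response is 80% with the marketed cream, strength has no effect at all, and the compounded cream is worse by d points for reasons of formulation. Pool the arms by strength (72 versus 72), test two-sided at 5%, and let p̄ be the mean of the two rates:

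Power = Φ{[d − 1.96·√(2·p̄(1−p̄)/72)] / √[(p₁(1−p₁) + p₂(1−p₂))/72]}

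- d = 5 points: about 11%
- d = 10 points: about 28%
- d = 15 points: about 52%

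These are the chances of a significant 8% versus 16% result when strength does nothing, against a nominal 5%. Neither the 80% nor any value of d comes from the Protocol. The example shows the mechanism, not an expected size.

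**The case against.** The strongest reply is that nothing is hidden and nothing randomised is invalid. The arm labels for G3 and G4 openly call the 8% cream compounded, and the Justification includes affordability. A comparison of the compounded cream with the marketed one may therefore be the practical question. This stands in part: G1 versus G3 and G2 versus G4 are valid comparisons of the treatments given. It does not rescue the objective, which speaks of concentration and does not carry the arm labels' qualification through.

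Several stronger readings are tempting, and the Protocol does not support them:

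- *The creams do differ in vehicle, stability or content.* Only the difference in manufacturer is documented. The rest is possible and undocumented. With an equivalent vehicle and verified content, the confounding could be negligible.
- *The planned analysis mislabels its factor.* The Results Analysis section names no ANOVA factors, and the Protocol contains no text of a planned conclusion. The wording to correct is that of the objective.
- *A product effect would rival the strength effect.* The Protocol gives nothing from which to size a product effect. The cited trial of strengths and incubation times shows complete-response gaps of 8 points at 3 h (85% versus 77%) and 2 points at 1 h (76% versus 74%). Those follow one or two treatments, whereas this trial gives one session. The same account gives 12-month recurrence of 17–19% with 16% against 44–45% with 8%, a much wider gap. Picking one of these figures as the yardstick would be selective.

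**Conclusion.** The point holds as a limit on attribution. Strength and product are completely aliased across all 144 planned participants, so the first half of the objective, read as a question about concentration, cannot be answered from these four arms by any analysis. Neither randomisation nor a larger sample changes this. A reader might infer that the 8% versus 16% comparison is worthless; it is not, since it remains a sound randomised comparison of two products.

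The incubation-time contrasts within each product are free of this confounding. An interaction between strength and time could not be told apart from one between product and time. The size of any product effect is unknown. The conclusion rests only on the arm definitions in section 3.9 and on the absence from the Protocol of any statement that the two creams share a vehicle or that the content of the 8% cream is assayed. The change should be made, because the objective as worded invites an attribution that the design cannot support.

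**What to change.** 1. In the Abstract and section 2.1, restate the first comparison as *compounded 8% MAL product versus marketed 16% MAL product*.
2. Add that neither a difference nor a similarity will be attributed to concentration alone unless an equivalent vehicle and assayed content of the 8% cream are documented. If such documentation exists, cite it in section 3.9.
3. Present 1 h versus 3 h within each product (G1 versus G2, G3 versus G4) as the contrast free of this confounding, and note that a strength-by-time interaction would equally be a product-by-time interaction.

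The cost is a change of text, with no new arm, participant or visit and no change to treatment. Documenting vehicle and content would need information from the pharmacy or an assay, and is required only if the trial team wishes to keep the claim about concentration. The downside is a narrower claim.
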